### Data integrity

Data will be entered by the participant directly in an online module, or by paper format and then entered by the research staff.

### Data analysis

Data from the trial will be compared based on the ’intention to treat’ principle. An intention to treat (ITT) analysis means that all patients, regardless of non-compliance, loss to follow-up or drop-out, remain in the analysis of the group to which they were randomized [17]. Depending on the mechanisms for missing data, the most relevant imputation method considering missing at random or not missing at random will be used in the ITT analysis [18]. A causal survival analysis measuring complier average causal effects (CACE), where standardization of baseline covariates (age, sex, Risser sign, major curve) and inverse probability weighting of post-randomization treatment adherence data is used in a per protocol analysis, to be contrasted with ITT results [19]. With basis in the COM-B model, patient reported capability and motivation can be hypothesized as potential mediators of treatment effect on the outcome variables. Fig 3 summarizes these causal inferences in a direct acyclic graph (DAG) model [20]. If a patient fails treatment and is offered another treatment, such as brace or surgery, the Cobb angle at the moment of commencing this treatment will be considered in the secondary outcome analysis of Cobb angle. Categorical parameters will be compared by the Chi-square test. Continuous and discrete parameters will be measured using parametric or non-parametric tests (depending on skewness) for group comparisons. Individual variables will be tested for their association with treatment effect by adding a predictor × treatment group interaction term to a regression equation. Additionally, Kaplan-Meier survival analyses will be used to display the probability of more than 6° Cobb progression over time. Cox regression or pooled logistic regression will be used to provide survival hazard ratios. The results will be reported according to Consolidated Standards of Reporting Trials (CONSORT) [21].

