### Subjects

Patients referred to the participating clinics are consulted and examined by a health-care provider specialized in spinal disorders. The magnitude of the scoliosis in the frontal plane is assessed by measuring the Cobb angle [12]. Upon inclusion, full spine frontal and sagittal radiographs, pelvic and hand radiographs will be taken. Up to three months old radiographs will be accepted. Fig 1 illustrates the flow process for included patients and Fig 2 illustrates the recruitment process. The following inclusion criteria will be applied:

Skeletally immature patients. Sander’s score ≤ 4 [13], Risser sign < 2 and no menarche for females.Age 9–15 years of age at inclusion.Primary curve of 15–24°.Apex of the primary curve at T7 or caudalScoliosis of idiopathic nature (i.e. no neuromuscular, congenital or syndromic origin).

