### Outcome measurements

Primary outcome measure is progression of more than 6 degrees in Cobb angle seen on two consecutive radiographs from baseline and during radiographic follow-ups. Radiographs (hand and standing full-spine frontal and sagittal) will be taken every twelve months and clinical follow-ups will be performed every six months until skeletal maturity. The endpoint failure of treatment is defined as an increase of the Cobb angle of more than 6° from the time of the first radiograph on two consecutive examinations, considered as the minimal clinically important difference [14]. If progression is suspected, additional radiographs may be taken for verification, also at additional time points not being considered as regular follow-ups. The number of patients progressing to a curve requiring brace treatment will be recorded and compared in both groups. Indication for brace treatment is progression of more than 6 degrees together with a primary curve ≥ 25 degrees and remaining growth.

Secondary outcome measures recorded at baseline and every six months for the entirety of the study include angle of trunk rotation, as measured with Bunnell’s scoliometer [15], SRS-22r and EQ-5D-Y quality of life questionnaires, VAS-pain, the International Physical Activity Questionnaire (IPAQ-SF) short form, Spinal Appearance Questionnaire (SAQ) and number requiring brace treatment.

In line with the capability, opportunity, motivation, and behaviour change model (COM-B) [16], to gain knowledge of behavioural outcomes, all study participants will answer three additional questions during each six-month follow-up; 1) the grade to which you feel that you have completed the treatment (adherence), 2) the grade to which you are motivated to carry out the treatment (motivation) and 3) how confident are you in your own capability to perform the treatment (capability). Additionally, the healthcare provider answers the question “to what grade the patient has adhered to treatment plan” (patient adherence). These questions are rated on a scale from best “very sure” (1 point) to worst “not at all” (4 points).

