**Fig 3 pone.0285246.g003:**
[figure not shown]
Directed acyclic graph of hypothesized mechanisms in single mediator models in the PREMISCOPRO trial and the estimated averaged effects standardized for baseline covariates and inverse probability weighted for post-randomization treatment adherence confounding. The indirect effect (*ab*-product) is the average intervention effect through the mediator. *a*, a-path (the intervention-mediator effect); *b*, b-path (the mediator-outcome effect); *c*, c-path (the total effect of the intervention on the outcome, without accounting for potential mediator); c′ (the direct effect of the intervention on the outcome, that works through all other mechanisms excluding the selected potential mediator).

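### The per-protocol standardisation set uses a Risser sign that entry cuts to two values and omits the baseline Sanders stage, so maturity confounding of unknown size may remain

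*Protocol article*

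**What the plan says.** The main comparison is by ITT after 1:1 randomisation. Beside it, the Data analysis section plans a causal survival analysis of complier average causal effects, with "standardization of baseline covariates (age, sex, Risser sign, major curve". The same sentence then describes a second layer of adjustment, this time for adherence: "inverse probability weighting of post-randomization treatment adherence data is used in a per protocol analysis, to be contrasted with ITT results". The Fig 3 legend describes the weighting as "inverse probability weighted for post-randomization treatment adherence confounding". The baseline set is named. The variables in the weight model are not.

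The Subjects section restricts maturity at entry by "Sander’s score ≤ 4 [13], Risser sign < 2 and no menarche for females", with the age criterion "Age 9–15 years of age at inclusion". At inclusion, "full spine frontal and sagittal radiographs, pelvic and hand radiographs will be taken". In follow-up, according to Outcome measurements, "Radiographs (hand and standing full-spine frontal and sagittal) will be taken every twelve months". The article does not say in words that the Sanders score is read from the hand film. That is a reasonable inference, and in any case the score must be known to apply the entry criterion.

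**The concern.** An entry rule that allows only Risser 0 or 1 leaves that covariate with a single contrast. The Sanders score, under its own limit, can still take up to four values. The plan therefore standardises on the marker that its entry rule has nearly emptied and leaves out a finer one that it already holds.

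This matters in an adherence analysis because adherence is not randomised, and the estimate relies on measured covariates to make adherers and non-adherers comparable. By the protocol's own logic maturity is prognostic: only skeletally immature children enter, participation ends at maturity, and remaining growth is part of the brace indication. Maturity at entry also governs how long a child must keep exercising, so a link with adherence is plausible, although the document gives no data on one. If both links exist, some of the difference between the per-protocol and ITT results could be a maturity effect that is read as an adherence effect.

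**Working it through.** **The plan's own figures.** The document gives no figure for residual confounding, no distribution of Risser or Sanders stage, and no relation of maturity to adherence. Its one computed figure is the sample size of 45 per group, on which this point does not depend. With 10% versus 39%, two-sided 5% (assumed) and 80% power, unpooled variance gives (0.10×0.90 + 0.39×0.61) × (1.960 + 0.842)² / 0.29² = 0.3279 × 7.85 / 0.0841 = 30.6, so 31. Then 31/0.80 = 38.75, so 39, and adding five gives 44, one short of the stated 45.

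**Step 1: the two markers at entry.** Risser below 2 gives two possible values and one parameter. Sanders 4 or below gives up to four values and up to three parameters. Only Risser is in the named set.

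**Step 2: what Risser alone could carry (all inputs assumed).** Share captured = between-Risser variance of failure risk / between-Sanders variance of failure risk.
- Stage mixes for stages 1–4: (10, 30, 40, 20), (25, 25, 25, 25) and (20, 40, 30, 10)%.
- Failure risks for stages 1–4: (60, 50, 35, 15)% or (35, 55, 45, 20)%.
- Risser 1 in 10% of stage 3 and in 25, 50 or 100% of stage 4.

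One case in full: equal mix, first risk pattern, Risser 1 in 50% of stage 4.
- Mean risk = 0.40. Between-stage variance = 0.25 × (0.20² + 0.10² + 0.05² + 0.25²) = 0.02875.
- P(Risser 1) = 0.25×0.10 + 0.25×0.50 = 0.15.
- Risk at Risser 1 = (0.025×0.35 + 0.125×0.15)/0.15 = 0.183. Risk at Risser 0 = (0.40 − 0.0275)/0.85 = 0.438.
- Between-Risser variance = 0.15×0.2167² + 0.85×0.0382² = 0.0083. Share = 0.0083/0.02875 = 0.29.

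Over all cases the share is 6–29% with Risser 1 in 25–50% of stage 4, and 43–71% if every stage-4 child is Risser 1. This ignores age and sex, which are in the set.

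**Step 3: adding age (all inputs assumed).** A simulation used a latent maturity score, Risser 1 in 10% or 30% of children with a latent correlation to maturity of 0.5–0.9, age correlated 0–0.8 with maturity, and Sanders in four classes with a latent correlation of 0.9. Share of maturity variance left unexplained:

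| Adjustment | Unexplained |
|---|---|
| Risser | 53–92% |
| Risser + age | 27–92% |
| Risser + age + Sanders | 17–28% |

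For Risser + age, by the age–maturity correlation: more than half is left at 0.3 or less, 45–70% at 0.5, 35–49% at 0.7, and 27–35% at 0.8. Adding Sanders lowers the figure in every scenario.

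**Step 4: how to enter Sanders stage.** Take the equal mix with the non-monotone risks (35, 55, 45, 20)%. Mean risk is 0.3875 and between-stage variance 0.0167.
- Linear term: covariance with stage = −0.0688, variance of stage = 1.25. Captured = 0.0688²/1.25 = 0.0038, which is 23%. For the other two mixes it is 38% and 8%. Under the monotone pattern it is about 97%.
- Two groups (1–2, 3–4): group risks 0.45 and 0.325. Captured = 0.0625² = 0.0039, again 23%.
- Three groups (1, 2–3, 4): group risks 0.35, 0.50 and 0.20. Captured = 0.25×0.0375² + 0.50×0.1125² + 0.25×0.1875² = 0.0155, which is 93%.

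**Step 5: room in the model.** Expected failures at 45 per arm: 45×0.10 + 45×0.39 = 4.5 + 17.6 = 22. After 20% dropout: 22 × 0.80 = about 18.

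**The case against.** The strongest reply has four parts.

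First, a reader might infer from Step 2 that most maturity confounding stays in the per-protocol estimate. The document does not support that. Step 2 leaves out age and sex, which are in the same list. It measures variance in risk, whereas confounding also needs a link between maturity and adherence, which no input supplies. In Step 3 less than half is left whenever age correlates at 0.7 or more with maturity. This reply stands in full.

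Second, there is a further adjustment layer, the adherence weighting. Its variables are not listed, and a journal article may leave them to the full plan, so Sanders stage cannot be said to be absent from the whole adjustment. This also stands, but it does not repair the baseline set, which the article does name.

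Third, the set is stated only for the per-protocol analysis. ITT rests on randomisation, and the article does not attach these covariates to its chi-square, Kaplan-Meier or Cox analyses. This stands and limits the scope.

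Fourth, with about 18–22 failures a short list is defensible, and a linear Sanders term may gain little (Step 4). This bears on how Sanders stage is entered and whether Risser stays. It is not a reason to prefer the two-valued marker over the finer one.

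**Conclusion.** The point holds as a weak choice in a list that the article itself fixes. The only direct maturity marker in the named set has two possible values, while a finer one required at entry is left out. Residual maturity confounding in the per-protocol/CACE estimate is possible, and its size is unknown. The range of 27–92% of maturity variance left after Risser and age rests wholly on assumed correlations. It describes lost information, not bias. Whether bias follows depends on a maturity–adherence link that the document does not report and on a weight model that it does not list. A claim that most of the confounding remains, or that the ITT result or the sample size is affected, would go beyond the text. The change is still worth making, because the marker is already held and the analysis has no randomisation to protect it.

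**What to change.** In Data analysis, add baseline Sanders stage to the standardisation set and state that it also enters the adherence-weight model, alongside Risser or in its place. Enter it as two or three grouped categories rather than as a linear term. Fix the grouping in advance from clinical reasoning and the baseline distribution, since Step 4 shows that a poor two-way cut can gain as little as a linear term. If the sponsor prefers to leave Sanders stage out, the reason should be stated. Either way, the decision should be dated before outcome data are seen, because a covariate added later would look data-driven.

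The cost is one or two extra parameters if Sanders is added beside Risser, and none or one if it replaces Risser, against about 18–22 expected failures. No new visit, film or measurement is needed.

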### Randomization procedure

After assessment, patients fulfilling the inclusion and exclusion criteria will be asked to give written and signed consent for participation. If the patient is aged less than 15 years, parental consent is also required. Patients who decline participation will be monitored as part of clinical routine.

Randomization will be done in a 1:1 ratio. Randomization will be performed using an online module available through the Swedish spine register (www.swespine.se). Randomization sequence have been prepared by an independent data manager at MedScinet (www.medscinet.com), the company that runs the register platform, and is unknown to the researchers.

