### Power analysis

The end point failure of treatment is defined as an increase of the Cobb angle of more than 6° on two consecutive x-rays, when compared to the x-ray performed at time of inclusion. Based on a hypothesized failure rate of 10% in the scoliosis specific exercise group and 39% in the observation group [6], with a significance level of 5% and a power of 80% and consideration for dropout of up to 20% and an additional adding of five individuals per group, an estimated number of 45 individuals in each group is required.

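### The intention-to-treat comparison of failure has no stated covariate adjustment, while the per-protocol analysis it is contrasted with does; this forgoes some precision and adds an avoidable chance difference to the contrast

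*Protocol article*

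**What the plan says.** Failure of treatment is binary: Cobb progression beyond the threshold on two consecutive radiographs (protocol article, Outcome measurements). The Data analysis section sets the ITT principle and states: "Categorical parameters will be compared by the Chi-square test". It adds Kaplan-Meier curves and Cox or pooled logistic regression for hazard ratios, without naming covariates for either model and without saying which analysis is primary.

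The same section describes a causal survival analysis of per-protocol type, "where standardization of baseline covariates (age, sex, Risser sign, major curve"), combined with inverse probability weighting for adherence. Its result is to be contrasted with ITT. The caption of Fig 3 applies standardisation for baseline covariates to the mediation models as well, and interaction regressions are planned.

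The Power analysis section uses two raw proportions, a "hypothesized failure rate of 10% in the scoliosis specific exercise group and 39% in the observation group", with "consideration for dropout of up to 20% and an additional adding of five individuals per group", and concludes that "an estimated number of 45 individuals in each group is required". The Randomization procedure section says only that "Randomization will be done in a 1:1 ratio"; no stratification is described. Eligibility (Subjects) requires "Risser sign < 2 and no menarche for females", a Sanders score of at most 4 and a primary curve of 15 to 24 degrees.

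**The concern.** Two things are at stake.

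The first is precision. The trial expects about 18 to 22 failures. If baseline curve size or maturity predicts progression, an unadjusted comparison leaves usable information aside, although the variables are already collected.

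The second is the contrast between ITT and per-protocol results. A reader will want to attribute a gap between them to adherence. If only one side is adjusted, part of any gap is the effect of adjustment on chance imbalance. If the ITT result is a comparison of proportions or a hazard ratio and the per-protocol result is a standardised survival effect, part of the gap may also be a change of scale.

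**Working it through.** **Inputs.** From Power analysis: failure 10% vs 39%, significance level 5% (two-sided assumed, since sidedness is not stated), power 80%, dropout 20%, plus 5 per group, 45 per group. From Randomization procedure: 1:1. Not given anywhere: how strongly the baseline covariates predict failure. That is assumed over a range.

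**Step 1: the plan's own figure.** Arcsine method: h = 2·asin(√0.39) − 2·asin(√0.10) = 0.705. Then n = 2(1.960 + 0.842)²/h² = 31.5, rounded up to 32; 32/0.8 = 40; 40 + 5 = 45. The stated figure reproduces as an unadjusted two-proportion design. Other conventions differ: 44 with unpooled variance, 48 with pooled variance, 55 with a continuity correction.

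**Step 2: power without adjustment.** Power = Φ[(0.29·√n − 1.96·√(2·0.245·0.755)) / √(0.10·0.90 + 0.39·0.61)].
- n = 36 (45 × 0.8): (1.740 − 1.192)/0.573 = 0.957, power 0.83.
- n = 45: (1.945 − 1.192)/0.573 = 1.316, power 0.91.

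Both exceed 80%.

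**Step 3: expected failures.** (0.10 + 0.39) × 36 = 17.6; (0.10 + 0.39) × 45 = 22.05.

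**Step 4: what adjustment would add.** Simulation with 4,000 trials per row, marginal risks held at 39% and 10%, full adherence and four independent covariates forming one prognostic score. The chi-square test is compared with a likelihood-ratio test from a logistic model with all four covariates. The last column is the SD, across trials, of the standardised minus the unadjusted risk difference.

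| Per arm | Log-odds per SD of score (approx. AUC) | Chi-square power | Adjusted power | Adjusted type I error | SD of difference |
|---|---|---|---|---|---|
| 36 | 0 (0.50) | 0.847 | 0.851 | 0.063 | 0.024 |
| 36 | 0.5 (0.63) | 0.854 | 0.872 | 0.054 | 0.030 |
| 36 | 1.0 (0.74) | 0.842 | 0.889 | 0.058 | 0.042 |
| 36 | 1.5 (0.81) | 0.833 | 0.915 | 0.065 | 0.051 |
| 45 | 0 (0.50) | 0.922 | 0.912 | 0.059 | 0.019 |
| 45 | 0.5 (0.63) | 0.919 | 0.920 | 0.058 | 0.025 |
| 45 | 1.0 (0.74) | 0.921 | 0.950 | 0.059 | 0.035 |
| 45 | 1.5 (0.81) | 0.929 | 0.967 | 0.067 | 0.043 |

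The change runs from −1 to +8 points of power. Part of the gain in the strongest rows reflects the adjusted test being slightly liberal: at 36 per arm and log-odds 1.5, its type I error is 0.065 against 0.048 for the chi-square.

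With two covariates and a standardised risk difference at 36 per arm, power rose from 0.84 to 0.873 (combined log-odds 0.8) and 0.909 (1.2), with type I error of 0.052 and 0.063. A separate run at 36 per arm gave about 0.85 rising to 0.86, 0.89 and 0.91 for log-odds 0.4, 0.8 and 1.2, with type I error of 0.054 to 0.062.

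**Step 5: the contrast.** In every row the standardised and unadjusted risk differences have the same mean, about −0.29, so neither is biased against the other. Within one trial they differ by chance with an SD of 0.02 to 0.05. Two SDs are 4 to 10 percentage points, against a design effect of 29.

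**Step 6: scale.** The marginal odds ratio is (0.10/0.90)/(0.39/0.61) = 0.174. With the same marginal risks, the covariate-conditional odds ratio is 0.132 at log-odds 1.0 and 0.098 at 1.5. A conditional ratio set against a marginal effect would therefore differ even with perfect adherence. Two marginal effects would not.

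**The case against.** The strongest reply is that the chi-square sentence is generic. It does not make that test the primary ITT analysis, regression models are planned alongside it, and their covariates may be listed in an analysis plan that is not shown. The randomised comparison is also unbiased without adjustment, whereas adherence is not randomised, so the per-protocol analysis needs covariates that ITT does not. All of this stands. What remains is that the article goes as far as naming the test, the covariates, the analysis that carries them and the contrast, and in that text adjustment appears on one side only.

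Several stronger readings are tempting, and the document does not support them:
- *The covariates serve only the per-protocol analysis.* They also enter the mediation models (Fig 3 caption).
- *The contrast is uninterpretable.* Standardisation yields a marginal effect, and so does an unadjusted randomised comparison. Step 5 shows that they agree on average.
- *The trial is underpowered without adjustment.* Step 2 shows 0.83 to 0.91. What is lost is a possible gain.
- *The predictors are strong.* No prognostic strength is given, and eligibility narrows the range of curve size and maturity. At an AUC of 0.50 to 0.63 the change is at most about 2 points.
- *Imbalance is likely.* The chance of exceeding 0.3 SD at 45 per arm is 2(1 − Φ(0.3/√(2/45))) = 0.155 per covariate, or 1 − 0.845² = 0.29 for at least one of two independent covariates. The nominal error rate of the chi-square test already allows for this.
- *Sanders stage should replace Risser sign.* Eligibility does leave Risser only the values 0 and 1, but nothing in the document shows that Sanders predicts progression better in this sample.

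**Conclusion.** The point holds as an improvement to the stated analysis, not as an error that threatens validity. The ITT comparison as described forgoes about 0 to 8 points of power. Where in that range the trial lies depends on an assumed prognostic strength (log-odds 0 to 1.5 per SD). The planned 80% is met either way under the protocol's own failure rates. The ITT versus per-protocol contrast carries a chance component with an SD of 0.02 to 0.05 on the risk-difference scale that matched adjustment would remove, and possibly a scale difference, because no common effect measure is fixed. The simulations assume full adherence and a binary outcome; they do not model varying follow-up.

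**What to change.** - State that the main ITT estimate of failure is covariate-adjusted, with a small prespecified set: baseline Cobb angle and one skeletal maturity measure. Two covariates suit the 18 to 22 expected failures.
- Report it as a standardised marginal risk difference, or as a standardised risk from the planned survival model, which accommodates follow-up that ends at maturity or progression. Use a robust or bootstrap standard error.
- Keep the chi-square test as a supporting analysis.
- Report the per-protocol/CACE effect on the same marginal scale, with at least the ITT covariates. Keep age and sex there, because adherence is not randomised and confounding has to be controlled. Sanders stage, already recorded for eligibility, may be added as a maturity measure.

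The cost is wording only, since all variables are already collected. The downsides are a slightly more complex analysis, a type I error slightly above nominal (about 5 to 6%), and little or no gain if the covariates turn out not to be prognostic.

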### End of study

The study will be terminated when the participant reaches skeletal maturity, defined as less than 1.0 cm growth of body height in six months, or if the curve progresses more than 6 degrees, compared to the baseline radiograph, seen on two consecutive spinal standing radiographs. In case of curve progression and a Cobb angle surpassing 25 degrees, treatment will be offered with standard TLSO or nighttime brace to be worn 20 hours and 8 hours, respectively, per day. In the event that a Cobb angle surpasses 45 degrees with risk for further progression, patients will be offered surgical treatment. Follow-ups will be done in similar way also for those failing treatment. Post-treatment follow-up after endpoint is planned to occur at 2, 5 and 10 years prospectively including full spinal frontal and sagittal radiographs.

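### Secondary outcomes recorded at baseline and every six months are compared by a group test chosen on skewness, with no baseline-adjusted or repeated-measures comparison named

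*Protocol article*

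**What the plan says.** All references are to the protocol article.

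- **Method.** Data analysis gives one rule for comparing continuous and discrete outcomes between arms: "Continuous and discrete parameters will be measured using parametric or non-parametric tests (depending on skewness) for group comparisons".
- **Data.** Outcome measurements schedules these outcomes repeatedly: "Secondary outcome measures recorded at baseline and every six months for the entirety of the study include angle of trunk rotation". The list goes on to SRS-22r, EQ-5D-Y, VAS pain, IPAQ-SF and SAQ.
- **Length of follow-up.** It differs by child. Subjects admits "Age 9–15 years of age at inclusion", and End of study says: "The study will be terminated when the participant reaches skeletal maturity, defined as less than 1.0 cm growth of body height in six months". Confirmed progression also ends participation. The same section adds: "Follow-ups will be done in similar way also for those failing treatment".
- **Analysis time.** None is named for the six-monthly outcomes. A child-specific time is given only for the Cobb angle in children who fail and are offered another treatment: "the Cobb angle at the moment of commencing this treatment will be considered in the secondary outcome analysis of Cobb angle".
- **Other models in Data analysis.** The baseline adjustment described as "standardization of baseline covariates (age, sex, Risser sign, major curve) and inverse probability weighting of post-randomization treatment adherence data" belongs to the per-protocol causal survival analysis, and its covariates do not include baseline questionnaire scores or trunk rotation. The interaction regression is for effect modification, the mediation models are for mechanism, and Kaplan-Meier with Cox or pooled logistic regression serves progression.
- **Missing data.** The analysis is by intention to treat, with an imputation method to be chosen according to the missingness mechanism.

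**The concern.** The method is stated, not left open, and it does not match the data structure. Each child contributes a baseline value and a series of follow-up values on each scale. A plain group test on follow-up scores uses neither the baseline nor the correlation between visits. The trial is sized on the binary progression endpoint only, so the patient-reported outcomes have no stated power margin. The Discussion nevertheless expects better self-image, mental health, capability and motivation with exercises.

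Letting skewness choose the test also leaves the effect measure open. A t-type test goes with a difference in means, a rank test with a shift in distribution. The quantity reported could differ from one scale to the next and would not be known before the data are seen.

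A further risk comes from variable follow-up. If the last available value were compared, children observed for different lengths of time would be set side by side.

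**Working it through.** **Sample size.** The plan's figure is 45 per arm, for the primary endpoint. With 10% against 39%, 5% (two-sided assumed) and 80% power, the arcsine formula gives h = 2·asin(√0.39) − 2·asin(√0.10) = 0.7055 and n = 2·((1.960 + 0.842)/h)² = 31.5, so 32. Then 32/0.8 = 40, and 40 + 5 = 45, which reproduces the plan. After 20% dropout, 45 × 0.8 = 36 per arm are evaluable. Only this 36 is carried forward.

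**Assumptions for the secondary outcomes.** The article gives no correlation, SD or effect size. I assume a correlation ρ of 0.3 to 0.7 between visits, equal variance at each visit, and a true difference of 0.5 SD.

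**Relative variance**, with the unadjusted follow-up score set to 1:
- change score: 2(1 − ρ)
- ANCOVA on baseline: 1 − ρ²
- ANCOVA relative to change score: (1 − ρ²)/(2(1 − ρ)) = (1 + ρ)/2

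**Power** = Φ(0.5/√(2v/36) − 1.96), where v is the relative variance. For v = 1 this is Φ(2.121 − 1.96) = 56%.

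| ρ | Follow-up score: v, power | Change score: v, power | ANCOVA: v, power |
|---|---|---|---|
| 0.3 | 1.00, 56% | 1.40, 43% | 0.91, 60% |
| 0.5 | 1.00, 56% | 1.00, 56% | 0.75, 69% |
| 0.7 | 1.00, 56% | 0.60, 78% | 0.51, 84% |

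ANCOVA therefore saves 9%, 25% and 49% of the variance against follow-up scores. Against change scores it saves 1 − (1 + ρ)/2, which is 25% at ρ = 0.5 and 15% at ρ = 0.7.

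**Several visits.** For a baseline-adjusted mean of k visits, v = (1 + (k − 1)ρ)/k − ρ². With k = 2 this is 0.56, 0.50 and 0.36 (power 81%, 85%, 94%). With k = 4 it is 0.385, 0.375 and 0.285 (93%, 93%, 98%). These figures need an effect that is constant over visits and a contrast averaged over them. They do not apply to a contrast at a single named visit.

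**Choice of test by skewness.** In 10,000 simulated null trials of 36 per arm, switching to a rank test when either arm's skewness exceeded 1 in absolute value (an assumed cut-off; the article gives none), the rejection rate was 5.1% for normal and 5.0% for lognormal data. The rank test was chosen in 2.1% and 96.6% of trials.

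**Last-value comparison, if it were used.** Assume 1.5 to 3 years to maturity (mean 2.25), failing children last seen at 1 to 1.5 years (mean 1.25), and no true effect at any given time. Failure then shortens follow-up by 1.0 year on average, and the spurious difference between arms is (0.39 − 0.10) × 1.0 × trend. For trends of 0.1, 0.25 and 0.5 SD per year this is 0.03, 0.07 and 0.15 SD. Simulated type I error (4,000 trials each) was 4.6%, 6.5% and 8.6%.

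**The case against.** The strongest reply is that the quoted sentence is short and general. It does not say that follow-up scores rather than changes are tested, nor that repeated visits are ignored. An article condenses its protocol, and the analysis visit, covariates and model form are commonly left to an analysis plan. This stands for the analysis visit, whose absence I do not count as a fault. It does not remove the point, because the article does choose a method, and a plan that used a baseline-adjusted model instead would depart from it. Change scores would use the baseline, but less efficiently than ANCOVA.

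Several stronger readings are tempting and not supported:
- **That the plan compares children at different follow-up lengths.** A child-specific time is stated only for the Cobb angle after failure. For the other outcomes a fixed-visit comparison is fully compatible with the text.
- **That children who leave are dropped.** Data analysis keeps all randomised patients in the analysis and provides for imputation, and End of study continues follow-up after failure.
- **That choosing the test on skewness inflates false positives.** The simulation showed no inflation.
- **That a stated power of 80% is being wasted.** The 80% belongs to the binary primary endpoint, and no power is claimed for secondary outcomes.

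It is also fair to say that a mixed model is one defensible choice among several, and that post-failure visits may include the effect of bracing. The article does not say outright that six-monthly questionnaires continue after failure.

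**Conclusion.** The point holds for the secondary continuous outcomes. The stated method gives up precision that the scheduled baseline measurements would provide at almost no cost, and it does not fix the effect measure in advance.

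The size of the loss depends on an assumed correlation and on which score the tests would use. At ρ = 0.3 against follow-up scores the saving is modest (9%). At 0.5 to 0.7 it is material under either reading. With 36 per arm and an assumed 0.5 SD difference, power rises from 56% to between 60% and 84% against follow-up scores.

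Unequal follow-up remains a conditional risk that naming a visit would close. It is not a planned analysis, and its size rests on assumed trends and timings. The primary endpoint has its own time-to-event analyses and is not touched. The change should be made, but the trial's main conclusion does not depend on it.

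**What to change.** Replace the sentence on parametric or non-parametric tests, for the continuous secondary outcomes, with a baseline-adjusted linear model:

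- Use ANCOVA on the outcome's own baseline value, or a mixed model over the six-monthly visits with baseline value, arm, visit and arm-by-visit.
- Name one visit, and make the adjusted mean difference at that visit the main contrast for every scale.
- For skewed outcomes, keep the same effect measure and use robust or bootstrap intervals instead of changing the test.
- Include visits after failure where they are recorded, in line with intention to treat. State that the existing rule for the Cobb angle after failure is a separate choice.

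The cost is a little more analysis work and no new data collection. The downside is reliance on missing at random for children with no observation at the named visit, for example those already mature. An early enough visit limits this.
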